# INTEGRA study protocol: primary care intervention in type 2 diabetes patients with poor glycaemic control

**DOI:** 10.1186/s12875-019-0916-9

**Published:** 2019-02-07

**Keywords:** Glycated haemoglobin, Clinical inertia, Intervention, Primary care, Type 2 diabetes, Treatment intensification

## Abstract

**Background:**

The management of hyperglycaemia and associated cardiovascular risk factors in patients with type 2 diabetes mellitus (T2DM) may reduce diabetes-related complications. The strategy to broaden the knowledge base of primary care professionals to improve health care has mainly been prompted by the current reality of limited resources and access to specialized care. The main objective of this study is to assess the effectiveness of comprehensive interventions focused on treatment intensification, decrease clinical inertia and reduce possible barriers to treatment adherence in patients with poorly controlled diabetes in a primary care setting.

**Methods:**

This is a two-phase mixed method study, whose aims are the development of complex interventions and the assessment of their effectiveness. The main study outcome is a change in glycated haemoglobin (HbA1c) levels.

The INTEGRA study is divided into two phases. Phase 1: A qualitative study with a phenomenological approach using semi-structured interviews with the objective of determining the factors related to the participants and health care professionals that influence the development and implementation of a specific intervention strategy aimed at patients with poor glycaemic control of T2DM in primary care. Phase 2: Exploratory intervention study to be conducted in Primary Health Care Centres in Catalonia (Spain), including 3 specific health care areas.

The intervention study has two arms: Intervention Group 1 and 2. Each intervention group will recruit 216 participants (the same as in the control group) between the ages of 30 and 80 years with deficient glycaemic control (HbA1c > 9%). The control group will be established based on a randomized selection from the large SIDIAP (Sistema d’Informació per al desenvolupament de la Investigació en Atenció Primària) database of patients with comparable socio-demographic and clinical characteristics from the three provinces.

**Discussion:**

This study is a comprehensive, pragmatic intervention based on glycaemic treatment intensification and the control of other cardiovascular risk factors. It is also aimed at improving treatment adherence and reducing clinical inertia, which could lead to improved glycaemic control and could likewise be feasible for implementation in the actual clinical practice of primary care.

**Trial registration:**

Clinicaltrials.gov. registration number. NCT02663245; January 25, 2016.

**Electronic supplementary material:**

The online version of this article (10.1186/s12875-019-0916-9) contains supplementary material, which is available to authorized users.

## Background

Type 2 diabetes mellitus (T2DM) is a chronic disease with a significant socioeconomic impact due to its high prevalence, the impact of associated complications, and high rate of mortality [1]. The elevated costs associated with the disease and its impact on patient quality of life are currently the target of many health plans and government strategies. The benefits of proper control of T2DM and the related cardiovascular risk factors, especially blood pressure and lipids, are widely accepted [2]. However, studies in Spain show that although evidence of the improved care of T2DM patients exists, the therapeutic goals are often not achieved in real-life clinical practice [3, 4].

A meta-analysis performed by Tricco et al. regarding the evaluation of strategies used in clinical trials for the improvement of quality procedures used in the management of diabetes shows evidence that the most notable improvements are observed when baseline levels of glycated haemoglobin (HbA1c) are high, especially over 8%, in diabetic patients [5]. This suggests that interventions should focus on patients with poorer control. With regard to strategies aimed at professionals and organizations that demonstrated efficacy, the most efficient were feedback from the information obtained in audits, training of professionals, and organizational changes (such as electronic records, clinical reminders, and case management, in addition to financial incentives).

Treatment adherence and clinical inertia play an important role in cases of insufficient glycaemic control. Therapeutic or clinical inertia is defined as the failure to initiate or to intensify treatment when indicated [6], thereby preventing or delaying the benefits of proper control. In the DIAMOND [7] study conducted in Spanish primary care centres, mean HbA1c was 8.1% over an average of 2.9 years, with values of > 7% before change, when switching from monotherapy to combination therapy was observed. Additionally, in an assessment of the GEDAPS group carried out in Catalonia, clinical inertia was detected in 33% of patients, and the mean HbA1c level to perform the treatment change was 8.4%. [8].

Sometimes, clinical inertia is related to the non-compliance of the patient [3, 9]. As seen in the Grant et al. [10] study, interventions oriented to improve patient adherence could consequently decrease clinical inertia. However, there are few studies on interventions aimed specifically at reducing clinical inertia.

Feedback to professionals is another possible key factor for improving clinical inertia. In an American study [11, 12], feedback was given to the professionals on the objectives achieved via alerts in the electronic records and/or weekly short meetings between professionals. As a result, treatment intensification increased from 35 to 52% in 3 years, and a significant improvement in HbA1c values (in the group receiving feedback, mean HbA1c was 7.5% vs. 8.2% in the control group) was also observed. However, in the Rochester study [13], although a reduction of more than 50% was observed in clinical inertia, this did not translate into an improvement in the control parameters after one year. Therefore, although interventions can be effective in reducing clinical inertia, they are not always effective in improving metabolic control.

Thus, there is a need to design strategies that help achieve the desired treatment goals that can be simultaneously implemented in real-life clinical practice in the primary care setting and the best way to achieve this goal is to use the mixed methodology by previously exploring the patients’ own perspective, in order to design a proper implementation strategy. Previous studies have shown that specialised Diabetes Unit improve glycaemic control [11]. Our main intervention was designed to evaluate if a local monographic consultation run by primary healthcare professionals could be effective in the context of real-world primary healthcare practice for the management of very poor controlled diabetic patients.

## Methods/design

### Aims of the study

Following this line of thought, the aim of this study is to assess whether glycaemic control improves in very poorly controlled type 2 diabetic patients as a result of interventions based on treatment intensification and on an increase in the patients’ adherence to treatment with a diabetes-targeted clinic specifically held for those patients.

The hypothesis is that in patients with inadequately controlled T2DM, a preliminary comprehensive detection intervention developed based on a monographic consultation interview and a complex intervention to improve the self-efficacy of patients could improve the effectiveness and cost-effectiveness in controlling glycaemia and other metabolic and risk factor parameters compared to the usual practice.

The secondary aims are to determine:The percentage of patients who achieve HbA1c levels of < 7% and < 8%.The improvement of lipidaemic control measured by the mean concentration of low-density lipoprotein cholesterol(LDL-C), non-high density lipoprotein cholesterol (non-HDL-C), and triglycerides in the intervention groups relative to the control group.Whether the percentage of patients who achieve target levels of LDL-C, non-HDL-C, and triglycerides recommended by the Catalan Health Institute guidelines (REGICOR tables) [14] is higher in the intervention groups than in the control group.Whether the percentage of diabetic patients with mean systolic blood pressure < 140 mmHg and mean diastolic blood pressure < 90 mmHg is higher in the intervention groups than in the control group.Whether the adherence to the screening for chronic complications associated with T2DM, according to the protocol of the Catalan Health Institute (fundoscopy, microalbuminuria, examination of the foot: arterial index and peripheral sensitivity), is better in patients who have participated in the specialized consultation unit than in the control group.Whether the patient’s self-efficacy to implement changes in risk factors is different in intervention group 1 (IG-1) than in intervention group 2 (IG-2).Whether the direct health costs of T2DM patients who participated in the monographic consultation are different from those in the control group.The impact on satisfaction and quality of life of patients.Whether the improvement in the control of behavioural cardiovascular risk factors (smoking and exercise) is better in the intervention than in the control groups.The improvement in the adequacy and intensification of treatment (clinical inertia).

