##### Study variables

The variables are collected at different time-points during the study (Table 1). These include: sociodemographic variables (age, sex), anthropometric variables (height, weight, BMI, blood pressure), clinical variables (drugs and dosages), smoking habits (smoking, non-smoker, ex-smoker), presence of multiple disorders (Clinical Risk Group and identified in the computerized patient clinical history and the number of health problems as a proxy asset of multi-morbidity), presence of microvascular complications (diabetic retinopathy, diabetic nephropathy, and diabetic neuropathy), presence of macrovascular complications (ischaemic heart disease, stroke, peripheral vascular disease, and heart failure), laboratory variables according to the standard procedures of the laboratory of reference (HbA1c, blood count, renal function- creatinine, glomerular filtration rate, urinary excretion of albumin), liver function (Alanine Aminotrasferase (ALT), Aspartate Aminotransferase (AST), alkaline phosphatase, Gammaglutamil transferase (GGT)), lipid profile (total cholesterol, HDL-C, triglycerides, LDL-C, and non-HDL-C), and episodes of severe hypoglycaemia (episodes of hypoglycaemia that require the intervention of a third party for recovery will be recorded).

**Table 1 Tab1:** Study timeline, variables and procedures

	IG-1 and IG-2					Control group	
Data collected	Assessment (months)				Source	Assessment	Source
	0	3	6	12		Month 0 & Month 12	
Inclusion/Exclusion criteria	1 + 2	1 + 2	1	1 + 2	e-CRF	§	SIDIAP
Sociodemographic variables and comorbidities: *1. Age, height, gender, weight, BMI, duration of T2DM, medication (active component and dose),* etc.*...* *2. Pluripathology, clinical risk group*	1 + 2	1	1	1 + 2	eCAP	§	SIDIAP
Main variable: HbA1c	1 + 2	1	1	1 + 2	e-CRF eCAP	§	SIDIAP
Lipid profile and other laboratory variables: Total cholesterol, HDL, LDL, triglycerides, non-HDL, urea, creatinine, glomerular filtration rate, urine albumin, AST, ALT, FA, GGT. Systolic and diastolic blood pressure	1 + 2	1	1	1 + 2	eCAP e-CRF	§	SIDIAP
Smoking habit	1 + 2	1	1	1 + 2	eCAP e-CRF	§	SIDIAP
Sedentary lifestyle	1 + 2	1 + 2	1	1 + 2	e-CRF		
Detection of macrovascular complications *Ischaemic heart disease, stroke, peripheral artery disease, heart failure*	1 + 2	1	1	1 + 2	eCAP e-CRF	§	SIDIAP

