Chronic microvascular complications detection *Diabetic retinopathy, diabetic nephropathy (albuminuria, renal failure), diabetic neuropathy*.	1 + 2	1	1	1 + 2	eCAP e-CRF	§	SIDIAP
Costs: *Cost of medication, laboratory tests, additional tests, cost of staff (visits), referrals, IT*	1 + 2			1 + 2	eCAP e-CRF	§	SIDIAP
*Costs:* *Urgent care, outpatient and hospital admissions*	1 + 2			1 + 2	e-CRF		
Satisfaction and quality of life of patients *DTSQ / ESDQoL*	1 + 2		1	1 + 2	e-CRF		
Professional Satisfaction *Specific Questionnaire*				1 + 2	e-CRF		
intensification/treatment adherence		1 + 2	1	1 + 2	e-CRF		
Occurrence of severe hypoglycaemia episodes	1 + 2	1	1	1 + 2	e-CRF		SIDIAP
“Patient Activation Measure” questionnaire (instrument for disease self-evaluation)	1 + 2	1 + 2		1 + 2	e-CRF		

*For the IG-1 (monographic + training of professionals + additional measures originated in phase 1), clinic visits will be carried out at baseline, 3, 6, and 12 months. For the IG-2 (training of professionals + additional measures originated in phase 1), clinic visits will be carried out at the time of inclusion (month 0), 3, and 12 months*

Variables related to healthcare costs are also collected and include the costs derived from the medication used (cost per patient per month of medication prescribed according to prices set by the Health Ministry), laboratory tests used (based on prices listed in the Catalan Health Institute service portfolio), supplementary tests, professional costs (the cost of patient visits), cost derived from the referrals to specialists, use of the emergency department, outpatient and hospital admissions, temporary disability, and consumption of testing strips for measuring blood glucose.

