
### Data collection

In the intervention groups (groups 1 and 2), sociodemographic, anthropometric, clinical, and laboratory variables are obtained from the clinical history and anamnesis of the subjects. The data obtained through the questionnaires are collected during the clinic visit according to the subjects’ responses. The variables related to health care costs are obtained from the SIDIAP database. In the control groups, all data will be obtained from the SIDIAP database.

For both groups, variables related to data are collected as described in Table 1 in the Electronic Case Report Form (e-CRF), specifically designed for the purpose of the study.

The consultation with the specialists is carried out in addition to any others that are deemed necessary, and the number and frequency of visits is derived from the interventions proposed to the patients (pharmacological and non-pharmacological).

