### Evaluation of the effectiveness in the three study groups

Data at baseline and at 12 months of the population of all three types of learning centres that meet the defined criteria for inclusion and exclusion will be compared. Criteria will be adequately defined using the ICD-10 codes, thoroughly specifying the temporary windows of the accepted values. Only the outcomes that include SIDIAP variables (as indicated in the Table 1) will be able to be evaluated; even those that are in the e-CRD will not be able to be assessed. This evaluation of effectiveness will be performed in two possible ways: i) following the patients who meet the inclusion criteria in 2015 until the end of the study in 2018 (cohort study), or ii) a cross-sectional study in 2015 and another in 2018.

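### The smoking comparison with usual care sets status scheduled at study visits against status retrieved from routine records, so changes are likely to be captured less completely in controls

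*Protocol article*

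**What the plan says.** The secondary aims of the protocol article (Aims of the study) include "Whether the improvement in the control of behavioural cardiovascular risk factors (smoking and exercise) is better in the intervention than in the control groups". Study variables defines smoking as a three-level status: "smoking habits (smoking, non-smoker, ex-smoker").

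The Table 1 row reads "Smoking habit 1 + 2 1 1 1 + 2 eCAP e-CRF § SIDIAP". Status is thus scheduled at months 0 and 12 in both intervention groups, and also at months 3 and 6 in IG-1, with eCAP and the e-CRF as sources. For controls the only source is SIDIAP, under a column for months 0 and 12. The note to the table adds that for IG-1 "clinic visits will be carried out at baseline, 3, 6, and 12 months", and for IG-2 "clinic visits will be carried out at the time of inclusion (month 0), 3, and 12 months".

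Under Data collection, the intervention groups' sociodemographic, anthropometric, clinical and laboratory variables "are obtained from the clinical history and anamnesis of the subjects", whereas "In the control groups, all data will be obtained from the SIDIAP database". The Control group section gives controls routine care only, and Study design places them in centres that do not take part.

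For the three-group evaluation, "Only the outcomes that include SIDIAP variables (as indicated in the Table 1) will be able to be evaluated". The Discussion describes SIDIAP as holding everything recorded in eCAP. The Statistical analysis plan section offers regression or propensity-score adjustment for differences seen at baseline.

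**The concern.** Smoking is a status that changes in the record only when someone asks and enters the answer. The plan creates an occasion for this at month 12 in IG-1 and IG-2 and none in the controls. A laboratory value that was not measured leaves a visible gap. An out-of-date smoking status looks like a valid value.

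If a control stops smoking and no one records it, the database still shows a smoker. A difference in recorded quitting between an intervention group and usual care could then reflect how often patients were asked rather than what the intervention did. The comparison is a stated aim, and the Discussion's limitations mention volunteer bias but not this.

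**Working it through.** **1. The plan's own figures.** The article gives no calculation for smoking. The group size comes from the HbA1c calculation: 42 × 1.7 = 71.4, rounded up to 72; 72 × 3 areas = 216 per group, as in the abstract. Only the 216 is used below.

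**2. Ascertainment side by side.**

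| | IG-1 | IG-2 | Controls |
|---|---|---|---|
| Smoking scheduled at a study visit | 0, 3, 6, 12 months | 0, 12 months | none |
| Source | eCAP, e-CRF | eCAP, e-CRF | SIDIAP |
| Occasion for a new entry near month 12 | study visit plus usual care | study visit plus usual care | usual care only |

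**3. Does using SIDIAP for all groups level this?** No. eCAP is a listed source for smoking at the intervention visits, and what enters eCAP reaches SIDIAP. The common database therefore carries the visit-prompted entries of the intervention centres, and there are no such entries in the control centres.

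**4. Does adjustment help?** No. Covariate and propensity adjustment act on differences between patients at baseline. The problem is how the month-12 outcome is recorded.

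**5. Possible size (illustration; every rate is an assumption, since the documents give none).** Let q be the true 12-month quit rate, equal in all groups, and r the share of control quits that are recorded. With all quits recorded in the intervention groups, the spurious difference is q(1 − r) and the apparent ratio is 1/r.
- q = 0.05, r = 0.8: 0.05 × 0.2 = 1 point; ratio 1.25.
- q = 0.10, r = 0.4: 0.10 × 0.6 = 6 points; ratio 2.5.

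With 95% of quits recorded in the intervention groups and q = 0.10, the difference is 0.10 × (0.95 − r):
- r = 0.8: 1.5 points, ratio 1.19.
- r = 0.5: 4.5 points, ratio 1.90.
- r = 0.3: 6.5 points, ratio 3.17.

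With 43 smokers per group, the chance of a significant result favouring one intervention group over controls is then about 4%, 12% and 24%, against a nominal 2.5%.

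**6. Against sampling error.** If 15%, 20% or 25% smoke at baseline, there are 216 × 0.15 = 32, 216 × 0.20 = 43 or 216 × 0.25 = 54 smokers per group. At a 10% quit rate and 43 per group, the standard error of the difference is √(2 × 0.10 × 0.90 / 43) = 6.5 points (7.5 with 32, 5.8 with 54). The 1-6 points correspond to about 0.01 × 32 = 0.3 to 0.06 × 54 = 3.2 patients per group.

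**7. Would counting only fresh entries cure it?** Not reliably. Assume a true control quit rate of 10%, with 50% of quitters and 30% of continuing smokers re-recorded. Fresh entries are then 0.10 × 0.5 = 0.05 quitters and 0.90 × 0.3 = 0.27 smokers, and the control quit rate appears as 0.05 / (0.05 + 0.27) = 15.6%. Carrying the last entry forward gives 5%. Here the two rules err on opposite sides of the true 10%.

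**The case against.** The strongest case against the point has five parts.

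- **No carry-forward rule is written.** The article promises time windows for accepted values, and window length is detail that a condensed article may leave out. This stands in part: one cannot say that an old entry will be read as the month-12 value. But the promise follows directly on the eligibility criteria and says nothing about smoking. If a window were applied, controls without a fresh entry would be missing, which is still unequal between groups.
- **Fresh questioning is not guaranteed in the intervention groups.** The reference to history and interview covers broad classes of variables, and eCAP is also a source, so some values may simply be read from the record. This is fair, but a scheduled item at a study visit remains an occasion that controls lack.
- **The direction is not fixed.** A reader might infer that controls look unchanged by construction and that the bias can run only towards the intervention. The documents do not support this. Routine visits may update controls. Relapse and uptake would also be missed in controls, which flatters them. A control who stopped before month 0 but is first recorded as an ex-smoker during follow-up would count as a quit.
- **The size is assumed.** A reader might also infer that the estimate would rest mainly on this artefact. It would not: over the 1-6 point range, sampling error is about as large or larger.
- **The design already names IG-2 as the control for IG-1**, with SIDIAP as an additional comparison. That is so, and it supports the fix. The smoking aim, however, is worded against the control groups.

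**Conclusion.** The point holds as one of unequal ascertainment and is minor. The protocol article itself fixes month-12 smoking status as a scheduled study item in IG-1 and IG-2 and as a retrieval from routine records in controls. Neither the SIDIAP-only rule nor baseline adjustment removes the difference. Quits are likely to be captured less completely in controls, which would probably favour the intervention.

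That direction is a judgement about which changes go unrecorded, and the documents do not settle it. The size cannot be derived either: the 1-6 points rest on assumed quit and recording rates and are comparable with or smaller than the standard error. What follows is that a favourable smoking result against usual care could not be told apart from more frequent asking. It does not follow that such a result would occur without a true effect.

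The point concerns the smoking half of one secondary aim and leaves the HbA1c outcome untouched.

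**What to change.** - Make IG-1 versus IG-2 at months 0 and 12 the lead comparison for smoking. Table 1 schedules status in both groups at those months, and Study design already treats IG-2 as the control for IG-1. Leave the additional IG-1 entries at months 3 and 6 out of this comparison.
- Label the smoking comparison with usual care exploratory.
- For that comparison, extract the entry date with the status and apply one common window around month 0 and one around month 12 in all three groups.
- Report, per group, the share of patients with a fresh entry in each window.
- Show the result twice: with older entries as missing, and with the last entry carried forward. Neither should stand alone, because restricting to fresh entries can itself select for quitters.

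The cost is a change of wording in the aim and analysis, and one more field in the extraction. There will be fewer evaluable controls, a wider interval and a weaker claim against usual care. The lead comparison also answers a narrower question, namely what the monographic consultation adds, and it remains non-randomised.
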